###### CONTENTS AT A GLANCE

- Summary
- Introduction
- Justification
- Objectives
- Materials and Methods
- Additional considerations
- Budget
- References

SUMMARY

Cysticercosis is a parasitic zoonosis caused by a tapeworm, *Taenia solium*, which infects both humans and pigs. *T. solium* causes serious diseases in humans and economic losses in endemic areas. Public health education has been reported to have a significant effect in reducing transmission of *T. solium* infections and it is likely to bring about long-term control of *T. solium* infections. Health education is suggested to be a priority even where other control strategies are intended. Since pigs are the primary intermediate hosts, they are obvious targets for the implementation of control measure. In addition, given the short life expectancy of the pig and the fact that it is difficulty to know when the infection occurs, the prevalence of porcine cysticercosis is a reliable indicator of active transmission zones. Effective health communication strategies require not only information on disease epidemiology and the characteristics of the technical intervention being promoted, but also social, cultural, behavioural, and economic data on the communities where the interventions will be implemented. In northern Tanzania, high prevalence of porcine cysticercosis was found following a study conducted in Mbulu district between 1998 and 1999. Lack of latrines, allowing pigs to roam, and lack of knowledge on the disease transmission were found to be factors likely contributing to the transmission of the disease in the area. Little is known on the economic losses occurring to farmers in Mbulu due to prevalence of porcine cysticercosis. Although the disease has been known by the farmers for many years, it is not known how the disease is perceived by the farmers. This information is necessary for evaluating the effectiveness of a control strategy in the area. The present study is intended to design and evaluate the effectiveness of a health education intervention for control of porcine cysticercosis in Mbulu district. The overall objective of the study is to reduce transmission of *T. solium* infections in humans and pigs in the area. The study will have three phases. Phase one of the study will be collection of anthropological data to aid in designing educational messages and study questionnaire relevant to the local context. Phase two will be designing and production of health educational materials. Phase three will be an assessment of the impact of the produced health educational materials in which a controlled randomised field trial will be conducted. The trial will have pre- and post-intervention examination of the study population in which both anthropological and epidemiological data will be collected for evaluation of the intervention. The community will participate in various activities during the research. The total duration of the study will be four years and three months effectively from July 2 000. The project will cost about US $ 93 739.97.

INTRODUCTION

Cysticercosis is a parasitic zoonosis caused by larvae of the tapeworm *Taenia solium*,which infect both humans and pigs. In humans the disease is called human cysticercosis whereas in pigs, it is called porcine cysticercosis. Human is the natural definitive host carrying the adult tapeworm in the small intestine. The adult worm causes a disease known as taeniosis that occurs when a person has eaten infected pork that may be raw or inadequately cooked. When the person ingests viable cysts from infected pork, the protoscolex evaginates in the intestinal tract and attaches to the mucosa of the small intestine, the proglottids develop from the neck of the protoscolex and mature as new ones are formed. Approximately three months after ingestion of the cyst, gravid proglottids start to appear in faeces, each containing about 60 000 eggs (Soulsby, 1982). Environmental contamination with infected human faeces is an important factor in sustaining the life cycle of *T. solium* (Schantz *et al.,* 1992). In the absence of treatment the adult worm may persist for up to 25 years in infected humans (Soulsby, 1982). This long-term holding of a person carrier of the tapeworm infection is of great epidemiological importance. It is known that invasive *T. solium* eggs may survive over six months in the external environment (Soulsby, 1982). The pig is the natural intermediate host harbouring the larval form of the parasite in the muscles and nervous tissues. Occasionally humans ingest the eggs of the parasite from faeces of infected humans through contaminated foods or water and develop human cysticercosis (Baily, 1996). When an intermediate host takes in eggs, onchospheres hatch in the small intestine and is activated under the influence of gastric and intestinal juices and penetrates the intestinal mucosa into blood and lymph vessels to be disseminated throughout the body. In pigs the onchospheres develop into larvae, *Cysticercus cellulosae* within 60 to 70 days (Miyazaki, 1991). Though the longevity of viable cysticerci is not known, the young age at which pigs are slaughtered means that the majority of cysts in pork would be viable.

The epidemiological cycle of *T. solium* occurs mostly in environments with low socio-economic or low hygiene levels, deficient sanitary facilities, or poor pig rearing practices where pigs can gain access to human faeces. Cysticercosis is most common in developing countries of Latin America, Asia, and Africa (Plancarte *et al.,* 1999). However, due to migration of people and tourism, human cysticercosis is now transmitted world-wide and it is considered as an emerging disease in the United States of America (Flisser *et al.,* 1998). Human cysticercosis has been reported in non pork-consuming communities such as the orthodox community in the USA (Schantz *et al.,* 1992). Studies on *T. solium* infections in Tanzania have largely been based on the infections in pigs, however, the possible medical implication of the parasite has been suggested by the presence of hospital records of human epilepsy and taeniosis in the studied areas ([name], 1999; Boa, unpublished report). A study conducted at household level in 21 randomly selected villages in Mbulu district northern Tanzania, established an overall prevalence of 17.4% (range 3.2-46.7%) of porcine cysticercosis in 770 live pigs examined by lingual examination ([name], 1999). This prevalence is higher than those reported by some similar studies in other highly endemic regions of the world. For example in Nigeria 5.5% of 1 300 pigs examined were found to be infected (Onah and Chiejina, 1995) while in Mexico, a prevalence of 4% was reported in 571 live pigs examined (Sarti *et al.,* 1992). Mbulu district was found to have a high potential for the spread of *T. solium* infections due to identified transmission factors. Out of 425 households observed, 21.6% did not have latrines. Of 198 respondents to interviews, 94.4% allowed their pigs to roam for food, and 41% of the respondents lacked knowledge on how a pig could acquire cysticercosis ([name], 1999). Thus, public health education could contribute in reducing the risk of this severe disease. Several studies have found that neither age nor sex of the pig had a significant association with the prevalence of porcine cysticercosis (Sarti *et al.*, 1992; Onah and Chiejina, 1995; Sakai *et al.*, 1998; [name], 1999). Studies in young pigs have indicated that infection rates are significantly higher in dry than in wet season (De-Aluja *et al.*, 1998; [name], in process). In the study in Mbulu, this was linked to the fact that during dry season pigs are let free to look for food in the fields since at this time crops have been harvested. On the other hand during wet season pigs are housed or tethered to restrict them from destroying crops in the fields. Seasonal prevalence of porcine cysticercosis should be considered when targeting and evaluating control measures.

*T. solium* is of public health as well as economic importance in endemic areas. When the larvae of *T. solium* infect the central nervous tissues of human they can cause various neurological symptoms. Epileptic seizures have been found to be typical symptoms when the brain of human being is infected (Sarti *et al.,* 1992). This condition is referred to as neurocysticercosis and may be fatal if left untreated. Porcine cysticercosis is thought to cause serious economic losses in the pork industry due to costs related to condemnation of infected carcasses. However, little has been investigated on the actual economic losses occurring due to these condemnations and whether farmers perceive these losses in endemic areas. Porcine cysticercosis prevents small-scale farmers in Mbulu from marketing their pigs because pig traders reject pigs with lingual cysts. However, the monetary or bartering losses to the farmers associated with the condemnation of infected pigs in the area is not known. Knowing the economic losses caused by condemnation of infected pigs would be important for cost-benefit analysis of the control program and hence decisions on whether or not to implement the program. This information would also be useful in showing the farmers that it is profitable to change their current traditional pig management practices. Cost-benefit analysis is also important when guiding the health authorities in setting priorities. It is apparent that people in Mbulu have been aware of the presence of porcine cysticercosis for many years (Boa *et al.,* 1995; Nsengwa and Mbise, 1995; [name], 1999). However, it is not known how the disease is perceived by the community. Studying people’s perception on the disease and its impact would help to know how much effort is required in the control of the disease. It is also the aim of the study to investigate if there are any social cultural, economic, and political factors that might cause barriers to community change.

Diagnosis of porcine cysticercosis in live pigs has been based on the examination of the under-surface of the tongue and by serology. Tongue examination has been found to be of a fair sensitivity and high specificity for field screening of porcine cysticercosis (Gonzalez *et al*., 1990). This method was found to detect up to 70% of truly infected pigs and it was 100% specific (Gonzalez *et al*., 1990). In Mbulu district (Boa *et al.*, 1995) and many other endemic areas (Sarti *et al*., 1992; Onah and Chiejina, 1995; Garcia-Noval *et al,* 1996) pig traders use the tongue examination method to reject owner’s pigs if they are found to harbour cysts under the tongue. Nevertheless, the predictive value negative of tongue examination is thought to be low since the method is less sensitive particularly in early or lightly infected pigs (Sciutto, *et al.*, 1998). Serology has been found to be relatively more sensitive compared to the tongue examination method (Gonzalez *et al*., 1990). Several serological methods have been developed elsewhere. However, most of these methods have limited application particularly in endemic areas due to passive transfer of maternal antibodies through colostrum, which have been found to persist beyond 8 months of pig’s age (Gonzalez *et al*., 1999). Therefore positive serology in endemic areas should be done with care when evaluating control strategies (Gonzalez *et al.*, 1994). Enzyme-linked immunosorbent assay (ELISA) method using purified antigen has been reported to be 100% sensitive and specific for human cysticercosis (Ito *et al.*, 1998) and it was reported to have similar efficacy in pigs. (Ito *et al*., 1999).

Different strategies have been advocated for the control of *T. solium* infections in endemic areas. These include treatment of infected humans or pigs, vaccination of pigs, general improved sanitation and industrialisation of pig rearing, and public health education (Plancarte *et al.,* 1999). Presently there is no vaccine available although there are promising progresses of finding a vaccine for porcine cysticercosis (Lightowlers, 1999). Despite the presence of effective drugs for both treatment of infected humans and pigs, strategies directed to the treatment of these hosts have limited applicability particularly in developing countries due to poor living conditions since the treated individuals are susceptible to re-infection (Lightowlers, 1999; Gonzalez *et al.,* 1999). Poor hygiene, economic constraints, and potential for re-introduction of the infections by migration of people are major problems that hinder the control strategies directed solely to treatment of infected hosts or general sanitation and industrialisation of pig rearing (Plancarte *et al.,* 1999). Studies carried out in Mexico for instance showed that there were no significant changes in porcine cysticercosis following treatment of human carriers of the adult tapeworm (Flisser *et al.,* 1998). Public health education is known to be valuable in reducing transmission of *T. solium* (Flisser *et al.,* 1998; Lightowlers, 1999)*.* This can be used alone or in combination with the other control strategies and in addition to controlling *T. solium* infections, it can reduce occurrence of other diseases related to poor hygiene such as cholera and typhoid fever. Public education has less economic demand, thus, can be implemented even in poor societies. Educational intervention is also important because it might bring permanent changes conducive to control and eventually eliminate the disease. Some educational interventions have shown significant reduction in the prevalence of porcine cysticercosis, significant changes in knowledge and some practices related to transmission of *T. solium* (Sarti *et al.,* 1997). A study in Mexico reported that after approximately one year post-intervention the prevalence of porcine cysticercosis decreased significantly (Sarti *et al.,* 1997). There is, however, lack of information on how public education can be effectively delivered to the target community. Various educational materials or communication channels such as radio programs, video, television, posters, books, pamphlets, and games can be used to educate farmers. Each medium has been found to have advantages and disadvantages, so using a number of methods to disseminate messages has been recommended to be more appropriate than relying on a single medium (Lloyd *et al.,* 1994). Effective health communication strategies require not only information on disease epidemiology and the characteristics of the technical intervention being promoted, but also social, cultural, behavioural, and economic data on the communities where the interventions will be implemented (Keilbach *et al.,* 1989; Lloyd *et al.,* 1994; Sarti *et al.,* 1997). Due to differences in social cultural, economic, and political settings in different areas of the world, there is a need to determine the effectiveness and sustainability of a control program in an endemic situation. The present study is intended to evaluate the effectiveness of a health education intervention in reducing transmission of *T. solium* infections in Mbulu district, Tanzania.

JUSTIFICATION

Pig rearing provides subsistence in many families in Mbulu district in northern Tanzania and is a source of animal protein in some other densely populated towns and cities of Tanzania such as Arusha, Moshi, and Dar es Salaam where most pigs from Mbulu are sold for slaughter and consumption. Before 1980s pigs from Mbulu were also exported to Kenya for commerce. However, porcine cysticercosis cut off the market in Kenya in early 1980s after the exported pigs were found to be infected (Mbulu district veterinary officer, verbal communication). Improving the health of the rural pigs in Mbulu would therefore improve the economic states of the rural farmers, increase food security in the district, reduce incidence of human taeniosis and cysticercosis, return the export opportunity, and improve the country’s economy.

Cysticercosis prevents small-scale farmers in Mbulu from marketing their pigs because pig traders reject pigs with lingual cysts. The monetary or bartering losses to the farmers associated with the condemnation of infected pigs in Tanzania is not known. Knowing the economic losses caused by condemnation of infected pigs would be important for benefit-cost analysis of the control program and hence a decision on whether or not to implement the control program. This information is also necessary to show farmers that it is profitable to change their current traditional pig rearing practices. Benefit-cost analysis is also important in guiding the government authorities when setting priorities. Mbulu district is found to have a high potential for the spread of *T. solium* infections due to identified risk factors such as lack of latrines, allowing pigs to roam, and poor knowledge on the mode of transmission of the parasite ([name], 1999).Thus, public health education could contribute to reduce the risk of this severe disease. It is apparent that people in Mbulu have been aware of the presence of porcine cysticercosis for many years ([name], 1999). However, it is not known how the disease is perceived by the community. Studying people’s perception on the disease is necessary in order to know how much effort is required in the control of the disease.

OBJECTIVES

**General objective:**

To reduce transmission of *Taenia solium* infections in humans and pigs in Mbulu district, Tanzania.

**Specific objectives:**

(i) To assess human perceptions and practices related to *T. solium* infections in the area.

(ii) To describe the epidemiology of porcine cysticercosis and assess its economic impact in Mbulu district.

(iii) To evaluate the effectiveness of produced health educational materials in improving human perceptions and practices related to the transmission of the disease.

(iv) To evaluate the effectiveness of the health educational materials in reducing the prevalence of porcine cysticercosis.

MATERIALS AND METHODS

##### Study area

Mbulu District is located in north-eastern Tanzania, between latitude 3.80o-4.50oS and longitude 35.00o-36.00oE. The altitude varies from 1000-2400 m above sea level. The area has a semi-arid and sub-humid climate and receives an annual rainfall of less than 400 mm and over 1200 mm respectively. The long rainy season extends from about March to Mid-May and the short rainy period extends from November to December. Relative humidity ranges from 55%-75% and mean annual temperature ranges from 15oC-24oC. The District has 59 villages and the 1997 District census showed that it had a population of 200 000 people and 32 883 pigs. Crop and livestock production is by far the most important economic activity, employing over 90% of the total District labour force. Most of the inhabitants are Iraqw tribe that occupies most of the highland areas and practices mixed farming. Pigs are raised in most households as a source of income and animal protein for the household. Most of the pigs are let free to graze particularly after harvesting. When there are crops in the fields most pigs are tethered at the backyard and are fed on cut grass, kitchen leftovers, pumpkins and maize grains. Few farmers house their pigs. Slaughtering of pigs takes place at home although few of the pigs are slaughtered at a nearby open slaughter slab. Some home slaughtered pigs are inspected by a meat inspector while some are not. Besides pig farming, villagers also raise other livestock including cattle, sheep, goats, and chicken. Some villagers keep dogs, cats, as well as donkeys.

##### Study design

This study will have three phases. Phase one will be a pilot study in which anthropological data will be collected to aid in designing appropriate educational messages and the study questionnaire. Phase two will be designing and production of health educational materials. Phase three will be an assessment of the impact of the produced health educational materials.

## Activities

## Phase

Collection of anthropological data to aid in designing relevant educational messages and study questionnaire

1

# 2

Designing and production of health educational materials

3

Dissemination and evaluation of health educational materials

Controlled randomized trial

Pre-intervention examination

Intervention

Post-intervention examination

-Perceptions

-Practices

-Prevalence of PCC

-Perceptions

-Practices

-Prevalence of PCC

Phase one - Pilot study:

A pilot study will be carried out in Mbulu district for the main purpose of collecting anthropological data to aid in designing appropriate health educational messages and study questionnaire. The pilot study will investigate the acceptance of the study by the community by making formal contacts with the local government authorities from the district to the village level to introduced the purpose of the study and seek permission to carry out the study. A meeting with study participants selected from each of the selected villages will be organised to ask for informed consent. Using key informants and participatory data collection methods, the pilot study will investigate community perceptions and practices related to *T. solium* transmission. The informants will be selected to represent farmers in different age groups and gender, health workers, pig traders, and veterinarians. Focus group discussions will be conducted consisting of the above categories. Each focus group will consist of six people and several group discussions will be conducted until sufficient information is attained. In-depth interviews will involve one person in each of the categories mentioned above. Therefore, a total of 7 individuals will be included in the in-depth interviews. The study will assess the local perception of the people about the disease, transmission, and control. The study will investigate whether the disease is perceived of any importance by assessing if there is any control effort that has been taken against the disease. The study will also investigate if there is any kind of action taken by the meat inspectors in case of infected pork and by health workers in case of taeniosis and epileptic patients. The community will be asked to give their recommendations for behavioural change and possible barriers. The village included in these anthropological studies will be excluded from the main study. The pilot study will also be used for informal testing of the questionnaire intended for the main study. A village extension agent will be selected in each village under study and trained by the researcher to be the health educator for the village participants. Updated census of pig farmers will be collected from the district to aid in deciding how many villages to be enrolled in the study.

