##### This will be a controlled randomised intervention trial with pre- and post-intervention examination of the study population. The pre-intervention study will be concerned with assessing the prevalence of porcine cysticercosis and its economic impact to the farmer. The study will also assess human perceptions and practices related to the transmission of *T. solium* infections in the area. Following the pre-intervention study, an intervention will be done in which participants in half of the selected villages will receive the health education while half of the villages will act as control. The village will be the unit of intervention allocation. Allocation of the villages to either intervention or control group will be done on a random manner or matched if randomisation will seem to favour communication between groups. Post-intervention study will be conducted to re-assess human perceptions and practices related to the disease, and the prevalence of porcine cysticercosis. The independent variables are therefore the prevalence of porcine cysticercosis, human perceptions and practices related to the disease, while the dependent variable will be the health education.

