# Allocation of villages to intervention:

Two groups will be compared whereby one group will receive the health education while the other group will act as a control. The villages will be grouped according to their similarities in their prevalence of porcine cysticercosis obtained during pre-intervention study and randomised within groups to either control or intervention.

Intervention:

Participants in the control group will follow their usual hygiene and pig management practices. For the intervention group, the educator in each village will organise and conduct two training sessions one- month interval. After the first session the educator will distribute pamphlets to the participants for further reference. The day after the session, the participants in the intervention group will watch a video program. The researcher will participate in the sessions as an audience, therefore the interventions in the selected villages will be planned such that the researcher will participate in all the villages.

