##### Ethical considerations

The researcher will ask for informed consent from the study participants before she can carry out the study. Confidentiality of the study participants will be adhered to. Ethical clearance will be requested from the National Institute for Medical Research ethical clearance committee in Tanzania. Research permission will also be requested from the researcher’s home institution (Sokoine University of Agriculture, Tanzania). After the end of the study the control group participants will receive the intervention. If the study participant or the family member is ill in our presence, she/he will be carried by the project vehicle to the health centre. If the animal of the study participant is sick the farmer will be advised to seek for the veterinary advice. If the intervention will be found effective it will be considered for the district.

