**Study limitations**

Due to the short period available for the data collection (about two years), it might not be possible to observe significant reduction in the disease prevalence. However, improvement in perceptions and practices related to the transmission of the disease will be used as intermediate outcomes to indicate reduction in the transmission of the disease.

Maternal antibodies due against porcine cysticercosis have been reported to persist beyond nine months of pig’s life. This may limit the use of ELISA or immunoblot tests that have been reported to respond on these antibodies. This is because we would like to detect actual cases (and not false positives due to maternal antibodies) and to be able to disentangle cases hat occured before and those that occurred after the intervention. Most studies on antigen ELISA for porcine cysticercosis are still under trial and some have reported that antigens are detected up to 200 days post-infection and tend to disappear afterwards probably due to formation of immune complexes.

We are not sure that we will get enough pigs for post-intervention study since we don’t know how prolific are the pigs in the study area. From the previous study, one farmer in Mbulu had an average of 1.8 pigs. Our aim is to examine a different population of pigs in the post-intervention from the pre-intervention study. This is because in this particular disease we cannot know the onset of the infection, otherwise we could include the pre-intervention population that had not been infected in the post-intervention study.

Due to the fact that the intervention is information based, leaking of information from intervention to the control group might be a problem. However care will be taken to have a clear geographical separation of the groups. In addition, participants in the control group will be assured well in advance that they will receive the intervention after the study in order to minimise chances of them seeking information from the intervention group. The researcher will investigate if there is any leakage of information from the intervention to the control group, or if there is any change in hygiene policy during the study period in order to take care of these during data analysis. [In this point I am still thinking if we can use blinding which is known to reduce bias]

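### As written, an extension agent in every study village is trained as health educator before allocation, so control villages may be exposed to part of the education through their own agent

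*Protocol*

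**What the plan says.** **Who is trained, and in which phase.** The only statement on training the educators stands in the Protocol under Phase one - Pilot study: "A village extension agent will be selected in each village under study and trained by the researcher to be the health educator". Study design describes that phase in these words: "Phase one will be a pilot study in which anthropological data will be collected".

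**When villages get an arm.** This happens in phase three, after the baseline survey. Allocation of villages to intervention states: "The villages will be grouped according to their similarities in their prevalence of porcine cysticercosis obtained during pre-intervention study and randomised within groups". The opening of Phase three adds that "participants in half of the selected villages will receive the health education while half of the villages will act as control".

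**What each arm is meant to get.** Under Intervention: "Participants in the control group will follow their usual hygiene and pig management practices". The delivery is described for the other arm: "For the intervention group, the educator in each village will organise and conduct two training sessions", followed by pamphlets and a video. Ethical considerations adds: "After the end of the study the control group participants will receive the intervention".

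**What is planned against contamination.** Study limitations accepts that "leaking of information from intervention to the control group might be a problem". It answers with geographical separation, an advance promise that controls will get the programme later, and a check for leakage between the groups. Post-intervention examination of the study population adds an item to the last questionnaire, asking controls whether education reached them from the intervention group.

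**The concern.** The trial tests information, so the contrast between arms depends on control villages not having it. If the agents of all study villages are trained before arms exist, the agents of the future controls (half the villages) are trained too. They are named as educators of their own villagers, and no instruction tells them to hold back until the study ends.

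Three things are at stake.

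- Any advice given in control villages shrinks the difference between arms, so an effective programme could look ineffective.
- The perception and practice scores are the most exposed outcomes, because they respond directly to information. Study limitations relies on them as intermediate outcomes if prevalence does not fall within the short study period.
- The exposure would go unrecorded. The leakage question asks about another source, so the planned allowance for leakage in the analysis would have no data on this one.

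If agents began to advise before the pre-intervention survey, baseline values could be affected as well.

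**Working it through.** **1. Order of events as written**

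| Step | Protocol section | Does an arm exist? |
| --- | --- | --- |
| Agent selected and trained, each study village | Phase one - Pilot study | No |
| Materials produced | Phase two | No |
| Baseline survey of prevalence, perceptions and practices | Phase three; Pre-intervention examination | No |
| Villages grouped on baseline prevalence and randomised | Allocation of villages to intervention | Yes, from here |
| Sessions, pamphlets and video, intervention arm only | Intervention | Yes |
| Reassessment; leakage question at the last interview | Post-intervention examination | Yes |
| Controls receive the programme | Ethical considerations | After the study |

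Training placed in the first row cannot be confined to villages that are identified only in the fourth.

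**2. Do the safeguards reach this route?** Distance between the arms does not act on an agent within a control village. The promise of later education is meant to stop control farmers seeking information from the other arm. The leakage check and the questionnaire item are both worded for information from the intervention group. None of them covers the control village's own agent.

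**3. The plan's own sample size** (Sample size calculation: 0.1464 against 0.1023, mean 0.1244, z values 1.96 and 0.84)

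n = (1.96 + 0.84)² × 2 × 0.1244 × 0.8756 / (0.0441)² = 878.20 per group. This reproduces the printed figure, which the plan rounds to 900.

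**4. Illustration of dilution.** Let controls gain a share f of the planned effect. The protocol gives no value for f; those below are assumptions.

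- Control prevalence: pc = 0.1464 − f × 0.0441
- Intervention prevalence: pi = 0.1023
- SE = √{[pc(1 − pc) + pi(1 − pi)] / 900}
- Power = Φ[(pc − pi)/SE − 1.96]

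| f | pc | Difference | SE | Difference/SE | Power |
| --- | --- | --- | --- | --- | --- |
| 0 | 0.14640 | 0.04410 | 0.01552 | 2.841 | 81% |
| 10% | 0.14199 | 0.03969 | 0.01541 | 2.576 | 73% |
| 20% | 0.13758 | 0.03528 | 0.01529 | 2.307 | 64% |
| 30% | 0.13317 | 0.03087 | 0.01518 | 2.034 | 53% |
| 50% | 0.12435 | 0.02205 | 0.01493 | 1.476 | 31% |

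Using a pooled variance under the null changes these results by about 0.1 of a percentage point (the 20% row moves from 63.6% to 63.5%). Like the plan's own formula, the calculation ignores clustering by household and village. Positive clustering would lower every row.

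**The case against.** The strongest reply is that the protocol keeps the education out of control villages. The sessions, pamphlets and video are described for the intervention group only, controls continue their usual practices, and they get the programme after the study. Training an agent does not in itself teach a farmer. This stands. A reader might infer that the control arm receives part of the intervention, but the text supports only a possible exposure.

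The second reply concerns timing. The training sentence carries no date and sits in a loose list of preparatory tasks. The materials are made only in phase two, and the number of villages is still to be settled from pilot data. Training in the final messages may therefore happen later than its position suggests. This stands in part: that the baseline survey follows the training is read from where the sentence is placed. But no other section gives a date. If later training is intended, the sections disagree and need reconciling.

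The third reply is that the phrase for study villages may loosely mean villages due to be educated, since Intervention speaks of an educator in each village when describing that arm. This is possible, but those villages are unknown in phase one, so the reading conflicts with the placement. Training control agents could also be preparation for the delayed programme, but that does not require it before follow-up ends.

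Finally, leakage is recognised and will be investigated. That is to the plan's credit, but the measures look only at information coming from the other arm. It is also tempting to argue that the agents live among the farmers and advise them as their daily work. The protocol gives only their title, and the point does not need that assumption.

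**Conclusion.** The point holds as a gap in the plan. Read as written, educator training covers all study villages and precedes allocation, and no safeguard prevents or detects education by a control village's own agent. Any such education would bias the comparison towards no effect.

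The conclusion rests on two readings: that the training sentence belongs to phase one, where it stands, and that it means all study villages, as it says.

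The size is unknown. The power figures should not be read as a forecast of this trial's power: they show what an assumed spill-over would cost, and at zero spill-over nothing is lost. They do show how little room there is. The design starts at about 81%, so a 10% spill-over already takes it below the 80% target.

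**What to change.** - In Phase one - Pilot study, limit the task to identifying the agents.
- Move the training to phase three, after the baseline survey and randomisation, and train only the agents of intervention villages.
- Train the agents of control villages after the final survey, when Ethical considerations already provides for controls to receive the programme.
- In Post-intervention examination of the study population, widen the leakage question to information from any source, naming the village's own extension agent.
- Bring Phase one, Phase three, Allocation of villages to intervention and Study limitations into line with this order.

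The cost is a change in the training schedule and one broader questionnaire item. It should be made before phase one starts, because training cannot be undone once given.
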